#### Secondary outcome measures

*Economic evaluation measures:* An economic evaluation will be performed if there is a statistically significant difference in RTW rates between the programs. The main outcome measure will be the incremental costs for an averted sick leave day in the two intervention groups compared to the reference group and in the inpatient program compared to the outpatient program. Data will be collected both through the administration of questionnaires and the extraction of records directly from the clinics. Health economic data will be collected 1 year after the participants’ initiation into the project. Subgroup analyses will also eventually be conducted.

A cost-utility analysis (CUA) will be performed by using a health-related quality of life questionnaire, the SF-12 version 2 [56], and converting the SF-12 scores to SF-6D scores. The SF-12 consists of 12 questions scored on 3- and 5-point Likert scales.

*Work ability:* Work ability will be measured with three items from the Work Ability Index (WAI) [57]. The participants will estimate their current work ability compared with their lifetime best ability. The score ranges from zero (cannot work at all) to ten (best work ability ever). The experienced work ability related to physical and psychological demands is scored on 5-point Likert scales. Work ability will be measured at all time points.

*Return-to-work self-efficacy (RTWSE):* RTWSE will be measured by the *Return-to-Work Self-Efficacy Scale* (RTWSE-19) [58, 59], which has three subscales: *meeting job demands* [7]*, modifying job tasks* [7] and *communicating needs to coworkers and supervisors* [5]. All items are scored on 10-point Likert scales.

*Fear avoidance for work:* Fear avoidance will be measured with a subscale from the *Fear-Avoidance Belief Questionnaire* [60, 61]. The scale consists of seven items and is scored on a 7-point Likert scale.

*Return to work expectations:* RTW expectations will be measured by one item from the WAI questionnaire: *Expectations of ability to remain in the present profession in 2 years*, with the response categories: *barely, uncertain and quite certain*. We will also use two questions from the *Fear-avoidance for work scale*: *I do not think that I will be back to my normal work within 3 months* and *I do not think that I will ever be able to go back to that work*, both scored on a 7-point Likert scale. We will also include an additional question measuring RTW expectations: *If you expect to return to work after occupational rehabilitation, after how long do you expect to return to work?,* with the response categories: *immediately or within 2 weeks, within 1 month, within 2 months, within 3 months, within 4 months, within 5 months, within 6 months, within 1 year, more than 1 year, never, and don’t know/uncertain*.

*Health and illness perceptions*: Health and illness perceptions will be measured with items from a variety of instruments. *General health* will be measured by one item from the SF-12, scored on a five-point Likert scale. *Subjective health complaints (SHCs)* will be measured with the SHC questionnaire [62]. This scale consists of twenty-nine items scored on a four-point scale from zero (no complaints) to three (serious complaints) and has 5 subscales: *musculoskeletal pain* (8 items), *pseudoneurology* (6 items), *gastrointestinal problems* (8 items), *allergies* (5 items), *and flu* (2 items). We will use the first 3 scales. Complaints will be reported for the last 30 days.

From the *Illness Perception Questionnaire* [63], we will include an open-ended response item asking the patients to list the three most important causal factors for their illness.

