The primary aim of the study is to evaluate whether there are any differences between the studied programs in the RTW success rates of the participating patients. Since both rehabilitation programs are complex and comprehensive, we hypothesize that there will be no overall differences in RTW rates but that some subgroups might benefit more from one or the other program. As earlier research has identified, there might be differences among subgroups based on gender; age; socioeconomic status; health complexity or severity; length of sick leave; job satisfaction; RTW expectations; the risk of job loss; and work-related strains such as demanding jobs, low decision latitude, conflicts, and poor support.Differences in cost-effectiveness will be evaluated if the programs show differences in RTW rates.The second aim of the study is to evaluate whether there are any differences between the programs in improvements in known modifiable obstacles to RTW, such as health and function, work ability, RTW expectations, RTW self-efficacy, and fear avoidance, among the participants.The third aim of the study is to examine the delivery and reception of the programs to understand how the interventions produce change. This aim will be achieved by investigating the clinicians’ evaluations of how the programs might work; the participants’ expectations of the program and how they respond to and interact with the interventions; and the effect of contextual factors on intervention mechanisms and outcomes in the RTW process, both at the individual and organizational levels.The fourth aim of the study is to explore key stakeholder views and experiences of RTW coordination. Key stakeholders are defined as patients, rehabilitation teams, employers, insurance case managers, general practitioners, and occupational health services.Our last two aims are to increase our understanding of any differences and similarities in the success of RTW outcomes for the participating clinics by combining the quantitative results for the primary objective of the study with the qualitative and quantitative results from the process evaluation in the study. An overarching aim is to support interactive learning between researchers and rehabilitation professionals for the development of program structures and practices that improve RTW outcomes for their patients.

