#### The program at the inpatient clinic

Three interdisciplinary teams are working with the RTW program at the clinic. Each team consists of a physician, a physiotherapist/psychomotor physiotherapist, a psychologist or a nurse, an occupational work consultant, and a sports pedagogue. One of them has the role of team coordinator. All teams and their patients also have access to a nutrition counselor, a riding instructor, and recreational instructors. Seventeen patients arrive at the clinic at the same time and stay for four consecutive weeks (36 h/week). The physician reads all the information in the referral papers sent from the patient’s general practitioner. In collaboration with the team, it is decided which team members will perform the first mapping conversation with the patient and who will be the coordinator during the patient’s stay at the clinic. The coordinator is responsible for a weekly meeting with the patient and decides whether the patient needs an individual therapeutic conversation with any of the other team members. The coordinator also contacts the employer and/or NAV. The team coordinates its activities and discusses approaches in regular team meetings. Individual goal setting and RTW planning are organized as a process in six group meetings during the stay. Visual tools are also used at the outpatient clinic to stimulate dialogue about the patient’s challenges and resources in the RTW process. The main part of the program is group-based physical activities such as gym, water exercise, psychomotor physiotherapy, climbing, Nordic walking, and other outdoor activities, which are led by sports pedagogues or physiotherapists. Different team members also give educational sessions in groups. The sessions cover themes such as the connection between bodily and psychological reactions, pain management, physical activity and training, introduction to mindfulness, diet and nutrition, and rights and responsibilities as an employee on sick leave. Communication with the patient’s employer and NAV consultant is usually done once during the stay by phone. For more details regarding the intensity of the intervention, see Table 2.

Description of the core components and intensity of the clinics, adopted from Costa-Black et al. 2013: 432 [15].

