#### Sample size

Estimation of the sample size is based on the assumption that approximately 50% of the patients will have a stable RTW, full-time or part-time, after 1 year. A two-sided survival analysis with a 5% level of statistical significance and 80% power shows that we will be able to detect a statistically significant difference between the programs at a hazard ratio of 0,73 with a sample size of 600 participants. Due to the lower capacity at the outpatient clinic, 200 participants will be recruited from the outpatient clinic and 400 will be recruited from the inpatient clinic.

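### The economic evaluation runs only after a significant RTW difference that the plan itself does not expect, so similar RTW would probably leave the cost comparison undone

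*Protocol article*

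**What the plan says.** The condition appears twice in the protocol article. Secondary outcome measures, under the economic evaluation, has: "An economic evaluation will be performed if there is a statistically significant difference in RTW rates between the programs". The Aims have a looser form that does not mention significance: "Differences in cost-effectiveness will be evaluated if the programs show differences in RTW rates".

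The economic paragraph covers two kinds of comparison: each program against a reference group, and inpatient against outpatient. The main measure is the incremental cost per sick leave day averted.

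The Aims also give the expected result: "we hypothesize that there will be no overall differences in RTW rates". The opening paragraph of the Aims says the study is meant to inform the choice of efficient and cost-effective programs.

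Three places state no condition. The paragraph that follows the condition says that a cost-utility analysis on SF-6D will be done. The section on cost-effectiveness/utility/benefit analyses sets out all three analyses. Appendix Table 4 schedules the incremental cost measure and the cost-utility analysis at 1 year.

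**The concern.** An economic evaluation estimates a cost difference and an effect difference jointly. Whether the effect difference alone passes a 5% test does not settle whether the evaluation is informative. Non-significance is compatible with a real difference, and if effects are truly similar the decision turns on cost. A utility measure may also differ between programs when RTW does not.

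Under the plan's own hypothesis the rule therefore leaves a stated purpose of the study unanswered. It also removes the contrasts with the reference group, which do not depend on whether the two programs differ from each other.

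There is a second, smaller problem. When the evaluation is triggered, the denominator of the cost-effectiveness ratio is an RTW difference from the same participants whose RTW result has just been selected for being significant. On average such an estimate is too large.

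**Working it through.** **Inputs, all from Sample size unless noted**
- Test: "A two-sided survival analysis with a 5% level of statistical significance and 80% power".
- Design effect and size: "at a hazard ratio of 0,73 with a sample size of 600 participants".
- Event rate: "approximately 50% of the patients will have a stable RTW, full-time or part-time, after 1 year", so 0.50 × 600 = 300 events.
- Allocation: "200 participants will be recruited from the outpatient clinic and 400 will be recruited from the inpatient clinic", so shares of 1/3 and 2/3.
- Intensity (Table 2 and the inpatient program section): 36 h/week for 4 weeks against 1–3 h/week for 3 months.

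**The plan's own figure.** By Schoenfeld's formula, events needed = (1.960 + 0.842)² / [(1/3)(2/3)(ln 0.73)²] = 357, or 714 participants at 50%. With 300 events the power at 0.73 is 72.9%, not 80%. If 50% is taken as the outpatient rate only, with 61.3% in the inpatient arm, there are 345 events and power is 78.7%. This mismatch is a separate matter and the point here does not rest on it. I use 300 events and show other counts below.

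**How often the evaluation is triggered.** SE(log HR) = 1/√(300 × 1/3 × 2/3) = 0.1225. Significance needs |log HR| above 1.96 × 0.1225 = 0.240, that is, an observed hazard ratio at or below 0.787 or at or above 1.271. With the estimate taken as Normal(ln HR, 0.1225²), the probability of significance and the mean size of a significant estimate are:

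| True HR | Evaluation triggered | Not run | Mean absolute log HR if triggered, relative to truth |
|---|---|---|---|
| 1.00 | 5% | 95% | undefined (mean size equals an HR of 0.75) |
| 0.90 | 14% | 86% | 2.9 |
| 0.85 | 26% | 74% | 1.9 |
| 0.80 | 45% | 55% | 1.5 |
| 0.73 | 73% | 27% | 1.18 |

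**Sensitivity to the event count.** Time to RTW is followed to 5 years and the condition names no time point, so more events are possible. At a true HR of 0.80:
- 345 events: triggered in 50%, inflation 1.41.
- 400 events (assumed): triggered in 56%, inflation 1.34.
- 480 events (assumed): triggered in 63%, inflation 1.26.

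At HR 1.00 the figure stays at 5% for any count.

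**Sensitivity to the number of tests.** Five RTW measures are listed under the primary outcome, and the condition does not say which one counts. If any of five independent tests could trigger the evaluation (an assumption), the chance under no difference is 1 − 0.95⁵ = 23%. Not running it remains the likeliest result.

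**Intensity.** The inpatient participants "stay for four consecutive weeks (36 h/week", so 4 × 36 = 144 h. Outpatient time, taking 3 months as 13 weeks, is 13 × 1 to 13 × 3 = 13 to 39 h. The itemised rows of Table 2, counting entries of more than 1 h as 1 h, give a narrower contrast: about 66–80 h inpatient (plus activities of varying length) against about 14–55 h outpatient. The inpatient program is the more intensive on either count, and the Interventions section says so too. Hours only indicate that a cost difference is plausible.

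**The case against.** **The cost-utility analysis may be unconditional.** The sentence announcing it carries no condition, and neither the analysis section nor Table 4 adds one. A reader might infer that the plan gives no economic result at all when RTW is similar, and the text does not establish that. But the sentence stands under the same economic evaluation heading, whose opening makes the whole evaluation conditional. What stands is that the scope is unclear.

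**The inflation factors belong to another quantity.** They are for the log hazard ratio of time to stable RTW. The economic measure is averted sick leave days, for which the article gives no standard deviation. This stands: the inflation carries over only as far as the two measures correlate, and it cannot be quantified from the document. A reader might also infer that every triggered ratio would be biased towards the better program. That is too strong. Selection inflates on average, only modestly at the design effect, and if one program is both better and cheaper the size of the ratio matters little.

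**The 5% assumes a clean single test.** The Limitations concede that referral bias cannot be eliminated, and such bias could produce significance with no true program effect. The real probability of triggering is therefore unknown. This stands as a limit on the figures, but does not make significance a better criterion.

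**Hours are not costs.** No unit costs are given, and much inpatient time is delivered in groups. A reader might take the hours ratio as a cost ratio, but the article does not support that.

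**It is a secondary evaluation under an openly stated rule.** This stands and limits the severity. The RTW comparison is untouched.

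**Conclusion.** The point holds. The rule makes the cost comparison depend on a result that the plan does not expect, and so works against a purpose that the plan states. It also removes the comparisons with the reference group for no reason connected with them, and it leaves the status of the cost-utility analysis uncertain.

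If the hypothesis of no overall difference is right, the evaluation is not run in 95% of studies. At the design effect it is not run in 27%. These figures assume a single unconfounded test on time to RTW, 300 events and 1:2 allocation.

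The inflation argument is secondary: it is real on average, large only for small true effects, and not quantified for sick leave days. The main objection does not need it. Severity: should be fixed.

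**What to change.** Delete the condition in Secondary outcome measures and in the Aims. State that the cost-effectiveness and cost-utility analyses are carried out on the 12-month data whatever the RTW result, for the comparison between programs and for each program against the reference group. Use the same confounder adjustment as for the RTW comparison. Report incremental cost and incremental effect with their joint uncertainty. If effects are similar, the cost difference with its interval is then the main result, not a reason to stop.

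The cost is extra analysis work and possibly some cost extraction from clinic records. Appendix Table 3 already schedules SF-12 and use of health services up to 12 months with no condition, and Data collection already provides for clinic data on program components and services.

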#### Additional measures

Personal and work-related conditions will be measured with questionnaires. If the origin of the measure is not mentioned, then the measure is adopted from a Norwegian national survey.

Personal-related questions and background variables include the following:
Gender, age, education, civil status, economy, life events, physical activity, etc.An adapted version of the *Adverse Childhood Experiences* (ACE) questionnaire [64].

Measures of work-related conditions include questions drawn from national surveys regarding the following:
Profession, industry, full time/part-time work, years employed, rank, type of work, working arrangement, type of contract and work accommodations, and expected type of work after rehabilitation.Experience of downsizing or restructuring at work and concern about losing one’s job.Functional ability and accommodations at work.Work characteristics, autonomy [8], social support [2], conflicts [2], job satisfaction [1], job involvement [1], and work commitment [1]. The measures are obtained from the *General Questionnaire for Psychological and Social Factors at Work* (QPSNordic) [65].*Effort-reward imbalance*. The measures are taken from the *Effort-Reward Imbalance scale* [66]. We use seventeen of the original twenty-three items across three scales: *effort, reward,* and *overcommitment.**Organizational support* [67]. We use twelve of the original thirty-six scale items.*Evaluation of health care services*. Questions regarding the evaluation of health care services are drawn from *The patient satisfaction questionnaire* developed by the Norwegian Knowledge Centre for Health Services [68]. Questions regarding the use of health care services are adapted from Norwegian national surveys. A new questionnaire was developed to evaluate rehabilitation interventions. Work on program theories at the two clinics, the description of program components, interviews with participants, and research on modifiable factors that can be approached in the interventions inspired the selection of the variables.

An overview of outcome assessments, questionnaire items, and timing are given in Tables 3–4 in the appendix.

### Data collection

Quantitative and qualitative data collection methods will be used.

We will obtain registry data from NAV on work participation, sickness benefits, work assessment allowances, and disability pensions. Data regarding labor participation and employment will be collected from the State Register of Employers and Employees administered by NAV or equivalent data from Statistics Norway. Data on education will be obtained from the National Education Database (NUDB). Information about diagnoses and treatments in specialist healthcare will be collected through the Norwegian Patient Registry (NPR). The participants will be followed from 2 years before inclusion until 5 years after their inclusion in the project via their registry data.

Survey data collection will be performed at baseline, the end of the program, and 6 and 12 months after the start-up of the program.

Data on program components, services, and epicrises will be collected from the clinics. Data associated with the participants’ evaluation of the program and their RTW processes will be collected via a survey, and from a group of approximately 40 participants. These participants were interviewed four times: at the start and end of the program and approximately 6 and 12 months after start-up.

Different methods will be used to collect data from the participating teams and key stakeholders (observations at the clinics, interviews, focus groups, and dialog meetings). For more details on the type of data collection that will be used for the process evaluation, please refer to the STAiR process protocol [51]. An overview of the outcome assessments and timing is given in the appendix.

#### Sample size

Estimation of the sample size is based on the assumption that approximately 50% of the patients will have a stable RTW, full-time or part-time, after 1 year. A two-sided survival analysis with a 5% level of statistical significance and 80% power shows that we will be able to detect a statistically significant difference between the programs at a hazard ratio of 0,73 with a sample size of 600 participants. Due to the lower capacity at the outpatient clinic, 200 participants will be recruited from the outpatient clinic and 400 will be recruited from the inpatient clinic.

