### Outcome measurements

#### Primary outcome measures

##### Return to work

*RTW* is our primary outcome measure, and it will be measured in different ways with registry data from NAV.
Cumulative number of sickness absence days. In line with Aasdahl and colleagues [55], the primary outcome measure is defined as the cumulative number of sickness absence days. By combining information from the different medical benefits, we will calculate the days on medical benefits (according to a 5-day work week) for every month during follow-up. Time on graded sick leave will be transformed into whole workdays. Days receiving sick-leave payment and work assessment allowance will be adjusted for the employment fraction, including a graded disability pension at inclusion. Any increase in the disability pension during follow-up will be counted as sick leave. The cumulative number of sickness absence days will be calculated at 6, 12, 24, and 60 months after inclusion. The evaluation of any subgroup differences will be based on this outcome.Time to stable return to previous or new work, full or partial, for at least 4 weeks without relapse. Time to RTW will be calculated as the number of calendar days measured from the start of the program until 5 years later.The proportions of workers at work full time or part-time, at baseline and every month after the start of participation in the program for 5 years.The proportion of workers who increase or decrease their work status or who have the same work status as they had at baseline. This outcome will be measured at 3, 6, 12, 24, and 60 months after baseline.Individual shifts between work, sick leave, and other social security benefits. This outcome will be monitored continuously based on registry data collected from 2 years before inclusion until 5 years after inclusion in the study [6].

To increase the external validity of the study, the RTW results for items one and two will also be compared to the results of a matched group drawn from the NAV registry.

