### Outcome assessment and evaluation

Cox proportional hazard models will be used to analyze the time until stable/sustainable RTW. Analyses will be performed for both full-time and part-time RTW. If there is an imbalance in any prognostic factors for RTW and this factor is strongly correlated with the RTW outcome, analyses of differences in RTW between the two clinics will be adjusted for prognostic dissimilarities if we have sufficient power [69]. To determine the probability of RTW, sick leave, other benefits, or disability pension, a multistate model can be established [70]. This model can determine whether there are differences in the patterns of RTW if differences in the results are discovered in the overall analyses. Since the primary outcome data are based on complete registry data, missing data should not be a problem.

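### On its plain reading, the sample-size statement gives about 73% power at HR 0.73 with 200 and 400 participants, not 80%; the hazard ratio detectable at 80% power is about 0.71

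*Protocol article*

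**What the plan says.** All the planning inputs stand in the Sample size section of the protocol article. It assumes that "approximately 50% of the patients will have a stable RTW, full-time or part-time, after 1 year". It then reports that "A two-sided survival analysis with a 5% level of statistical significance and 80% power" allows the study to "detect a statistically significant difference between the programs at a hazard ratio of 0,73 with a sample size of 600 participants". The next sentence, giving lower outpatient capacity as the reason, sets the groups: "200 participants will be recruited from the outpatient clinic and 400 will be recruited from the inpatient clinic".

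The section gives no event count, formula or follow-up horizon. It does not say whether the power figure already allows for the unequal groups.

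Two other places bear on the point. Under Outcome assessment and evaluation, "Cox proportional hazard models will be used to analyze the time until stable/sustainable RTW". Under Primary outcome measures (Return to work), "Time to RTW will be calculated as the number of calendar days measured from the start of the program until 5 years later". The planned follow-up is therefore 5 years, while the sample-size assumption is given at 1 year only.

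**The concern.** The section states both its inputs and its result, so the result can be checked, and on the plain reading the two do not agree. In a two-group survival comparison, power depends on the number of events and on how participants divide between the groups. A 1:2 split carries less information per event than equal groups. Here the split appears only after the power claim.

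What is at stake is how a non-significant comparison is read. The Aims section hypothesizes no overall difference in RTW rates, so a non-significant overall result is the one the authors expect, and readers will look to the stated sensitivity when they interpret it. At 73% power, the chance of missing a true HR of 0.73 is 27%, not 20%.

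**Working it through.** **Inputs (Sample size section):** two-sided alpha 5% (z = 1.960); power 80% (z = 0.842); HR 0.73, so |ln HR| = 0.3147; N = 600; 50% stable RTW at 1 year; groups of 200 and 400, so p = 1/3 and p(1−p) = 2/9.

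**Derived:** reading the 50% as all patients, D = 0.50 × 600 = 300 events. This count is not stated in the article.

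**Formulas (Schoenfeld):**
- Power = Φ(√(D·p(1−p)) × |ln HR| − 1.960)
- Events needed = (1.960 + 0.842)² / [p(1−p) × (ln HR)²]
- Detectable HR at 80% power = exp(−2.802 / √(D·p(1−p)))

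**Step 1. Try to reproduce the stated figure with equal groups.**
- Power = Φ(√75 × 0.3147 − 1.960) = 77.8%
- Detectable HR = exp(−2.802/8.660) = 0.724
- Events needed for 80% at HR 0.73: 317, or N = 634 at 50%

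This is close to the stated 80% and 0.73 but does not reach them.

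**Step 2. Use the planned 200:400 split.**
- Power = Φ(√66.7 × 0.3147 − 1.960) = 72.9%
- Detectable HR = exp(−2.802/8.165) = 0.710
- Events needed for 80% at HR 0.73: 357; 357/600 = 59.5%

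**Step 3. Divide the shortfall.** The total is 80 − 72.9 = 7.1 points. Of these, 80 − 77.8 = 2.2 are already missing with equal groups, and 77.8 − 72.9 = 4.9 come from the split.

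**Step 4. Check other methods (300 events, 200:400, two-sided 5%).**

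| Method | 400-participant clinic faster | 200-participant clinic faster |
|---|---|---|
| Freedman | 67.8% | 76.7% |
| Wald, arm-specific events | 69.2% | 75.5% |
| Log-rank simulation, 4,000 runs | 70.7% | 75.7% |

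With 300 events, none of the two-sided calculations tried reaches 78%, even with equal groups. A one-sided 5% test at 200:400 would give 82.2%, but the article says two-sided.

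**Step 5. Read the 50% as one program's rate.** If 50% is the slower program's rate, the faster program has 1 − 0.5^(1/0.73) = 61.3%. At 200:400:
- 400 in the faster program: D = 200 × 0.50 + 400 × 0.613 = about 345. Schoenfeld power is 78.7%, detectable HR 0.726.
- 200 in the faster program: D = 400 × 0.50 + 200 × 0.613 = about 323. Freedman gives 79.6% (HR 0.729) and Wald 78.3% (HR 0.725).
- Other method and direction combinations give 74 to 76% by formula.

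With equal groups the same reading gives 82.0% (Schoenfeld) or 81.4% (Freedman). If 50% is instead the faster program's rate, 200:400 gives 65 to 70%.

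**Step 6. Count events after 1 year.** Schoenfeld power at 200:400 is 80.4% with a 60% event share (360 events) and 86.0% with 70%. The article gives no event share beyond 1 year. As an illustration only, a constant hazard with 50% at 1 year (an assumption) would reach 59.5% at about 1.3 years.

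**The case against.** The strongest reply is that the stated figure can be approached with the planned split. If the 50% is the slower program's rate and the smaller clinic is faster, the Freedman formula gives 79.6% power and a detectable HR of 0.729, which round to the published values. The 50% is also approximate and tied to 1 year, while time to RTW is followed for 5 years, and an event share near 60% restores 80%. Both arguments stand as far as they go: the figure cannot be called wrong under every reading, nor 80% unreachable. Neither rescues the sentence as written, because it attaches the 50% to the patients as a whole and names no later event share or horizon.

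A reader might also infer more than the article supports:
- *That the unequal split was overlooked.* The article does not say how the calculation was done. Equal groups with 300 events do not reproduce 80% either, so the split is only part of the gap.
- *That a null result would be presented as excluding HR 0.73.* The article speaks only of being able to detect it, and its Limitations section concedes that the nonrandomized arms cannot settle whether the programs differ in effect.
- *That the economic evaluation hangs on this Cox test.* The Secondary outcome measures section makes it conditional on a significant difference in RTW rates and names no test.
- *That covariate adjustment will lower power by a known amount.* Adjustment is conditional under Outcome assessment and evaluation, and the article gives no figure from which to compute such a loss.

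**Conclusion.** The point holds on the plain reading. With 50% of all 600 patients as events, a two-sided 5% test and 200:400 groups, power at HR 0.73 is about 73% (68 to 77% by formula and direction), and the hazard ratio detectable at 80% power is about 0.71. About 5 of the 7 missing points come from the split and about 2 precede it.

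The conclusion rests on two assumptions: that the 50% refers to all patients, and that only events within the first year count. If the authors meant otherwise, the stated figure may be nearly right or even conservative, but the article would then need to say so. The change is modest, from HR 0.73 to about 0.71. It alters no analysis or design feature, so this is a worthwhile correction rather than an essential one.

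**What to change.** Revise one sentence in the Sample size section, for example: *With 200 and 400 participants and 50% stable RTW overall at 1 year (about 300 events), the study has about 73% power at HR 0.73 and 80% power at HR of about 0.71.*

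If a different event share, a one-program reading of the 50% or a longer horizon underlies HR 0.73, state it and give the power that matches it at 200:400.

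The cost is one sentence and a slightly less favourable figure. No extra enrolment is needed.
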